**Discussion:**

Stigma must be addressed in the criminal legal system to facilitate the uptake of evidence-based addiction care. This study is the first to evaluate a stigma intervention designed for the criminal legal setting and results will be used to inform a larger, randomized controlled trial. The rationale for this study, research design and measures, as well as potential implications for the field are described.

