#### Primary staff outcomes

We will examine change from the baseline to the three-month follow-up timepoint in the following measures:Perspectives on Stigma Reduction. The Perspectives on Stigma Reduction scale (PSR) is a 24-item internally developed measure that assesses perspectives on stigma (e.g., importance, impact on people involved in the criminal legal system) and stigma reduction strategies (e.g., openness to learning new strategies, use of nonjudgmental behaviors), among criminal legal professionals. 20 of the items are rated on Likert scales ranging from 1 (strongly disagree) to 9 (strongly agree), and 4 items are rated on a scale from 1 (0% of the time) to 9 (100% of the time). Items with the same response scales are summed to create total composite scores. Higher scores indicate more favorable views about stigma reduction.Difference and Disdain. The Difference and Disdain scale (DaD) (Corrigan et al., 2015b) is a 9-item measure that assesses how individuals view others in stigmatized groups compared to the general population. Responses are rated on a scale from 1 to 9, where 1 represents a belief that stigmatized people are similar to/favorable compared to others in the general population and 9 represents a belief that they are different from/unfavorable compared to the general population. We adapted this measure to ask about people with substance use problems and then criminal involvement (18 items total). Each scale ranges from 9–81 with higher scores indicating more differences/disdain. This measure has been shown to be valid for assessing public stigma in multiple studies (Corrigan, 2017; Corrigan et al., 2021).Social Distance. We use 10 items to assess desired social distance from people with a criminal background (separately asking about violent and nonviolent criminal histories) and 5 parallel items to assess desired social distance from people with histories of addiction. Items were adapted from the Bogardus social distance measure (Bogardus, 1933) to capture how staff would feel about interacting with (e.g., working, living next to, talking to, marrying) people with these backgrounds. Responses are rated on a Likert scale ranging from very uncomfortable to very comfortable, with the total score ranging from 10 to 50. Higher scores indicate less desired social distance. Variations of the Bogardus social distance items have been used widely and demonstrate good reliability and validity among various samples (Compton et al., 2006; Geisinger, 2010).Stigmatizing Attitudes Toward Criminal Involvement. The Attitudes Toward Prisoners scale (ATP) (Melvin et al., 1985) is a 36-item measure that assesses attitudes, beliefs, and negative stereotypes about “prisoners,” with responses rated on 5 point Likert scale from disagree strongly to agree strongly. We changed the word prisoners to “justice-involved people” throughout the scale to remove stigmatizing language but also because the staff we are targeting primarily work with people who are not currently incarcerated. Negatively worded statements are reverse coded for a summed total score ranging from 36 to 180. Higher scores indicate more positive attitudes toward people involved in the criminal legal system. The ATP has been used widely with criminal legal staff samples and demonstrates good internal consistency and validity (Kjelsberg et al., 2007; Ware et al., 2012).Beliefs About Addiction. The Addiction Beliefs Inventory (ABI) (Luke et al., 2002) is a 30-item measure containing 8 subscales that assess how people think about substance use, including beliefs about controllability, the disease model of addiction and genetic susceptibility, the need for professional treatment, how responsible someone with substance use is for their actions and recovery, self-medication, and beliefs about addiction being a moral weakness. Responses are rated on a 5-point Likert scale ranging from strongly disagree to strongly agree, with higher scores representing more agreement with the beliefs represented in the subscale. The ABI is often analyzed as subscales rather than a total score and demonstrates acceptable reliability and validity in multiple studies (Jordan et al., 2002; Luke et al., 2002).Opinions about Medication for Opioid Use. An adapted version of the Opinions about Medication-Assisted Treatment scale (aOAMAT) (Friedmann et al., 2016) will be used to evaluate how staff think about the treatment of OUD with methadone and buprenorphine among legally-involved populations. Responses are rated on a 6-point Likert scale (1 = strongly disagree, 5 = strongly agree, and we added a sixth response option if they had never heard of the medications). Methadone and buprenorphine were included in the same item to reduce the measure’s length, and naltrexone was not included (e.g., “Methadone and/or buprenorphine should be available as a lifelong treatment option”). This collapsed the 18 original items into 9; 2 additional items were added regarding the administration of medications during incarceration. This adapted measure has been shown to be reliable and valid with criminal legal staff ([name] et al., 2022).

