#### Primary client outcomes

We will examine change from the baseline to the 3-month follow-up timepoint in the following measures:Self-stigma. We will use the Substance Abuse Self-Stigma Scale (SASS) ([name] et al., 2013) to assess self-stigma associated with substance use and criminal involvement. The SASS is a 41-item measure that assesses self-devaluation, fear of experiencing stigma, avoidance of stigma, and values disengagement among people with substance use problems. Responses are rated on a scale from 1 (never or almost never) to 5 (very often), with total scores ranging from 41 to 205 and higher scores indicating more self-stigma. We adapted this measure to ask about both criminal involvement and substance use stigma within the items in this measure (e.g., “People think I’m worthless if they know about my substance use or criminal history”). The SASS scale has been shown to be reliable and valid for assessing self-stigma among people with substance use problems (Brown et al., 2015; [name] et al., 2013).Shame. The Internalized Shame Scale (ISS) (Cook (n.d.)) is a 24-item measure that includes shame-related thoughts and experiences, which are considered central to self-stigma. Responses are rated from 0 to 4, where 0 is never and 4 is almost always, with the total score ranging from 40–120 and higher scores indicating more internalized shame. The ISS has been used to track changes in shame across clinical interventions, including ACT for substance use self-stigma ([name] et al., 2013) and is shown to be reliable and valid in a variety of clinical and non-clinical samples (Goffnett et al., 2020; Rybak & Brown, 1996).Self-efficacy. We use a 1-item internally developed measure to assess the degree to which clients feel they can cope with unfair judgments from the community regarding their substance use or criminal history. The item is rated on a scale from 1 to 10, with 1 being lowest expectation of success and 10 being the highest expectation of success.Coping skills. We use 28 items from the Dialectical Behavior Therapy Ways of Coping Checklist (DBT-WCCL) (Neacsiu et al., 2010) to assess client use of specific skills being taught in the CSTARR-client intervention. The DBT-WCCL is originally a 59-item measure that captures client use of adaptive and maladaptive coping skills and is widely used among people attending DBT skills interventions, which is another third-wave behavioral therapy similar to ACT. This measure has been used to assess improvement across treatment among people with various degrees/severity of mental illness (Brown et al., 2019; Kells et al., 2020; Stein et al., 2016). We utilize items that capture skills being taught in CSTARR-client (e.g., engaging in valued actions, acceptance of thoughts and feelings, emotion regulation techniques such as relaxation) as well as maladaptive coping skills we believe CSTARR-client may reduce, such as externalization of blame, avoidance, and social withdrawal/isolation.

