### Data analysis plan

#### Preliminary analyses

All data will be entered directly into the Redcap survey platform (directly by staff completing the online survey, via research staff manual entry during phone interviews with clients). Data will be exported, cleaned, and managed using Statistical Package for the Social Sciences (SPSS). Data from all counties will be pooled for staff and client assessments. We will run descriptive statistics (i.e., ranges, means, frequencies) and transform variables to achieve normality as needed.

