#### Effectiveness

Pre- to post- change in staff and client assessments will be analyzed using repeated measures factorial ANOVAs that compare pre, post-, 1-month, and 3-month follow-up data for clients and staff. Tukey’s posthoc comparisons will be used to pinpoint significant mean differences between timepoints. We will examine main and interaction effects to test whether mean differences in staff assessments depend on type of profession (assuming adequate sample sizes). Omega squared effect size estimates will be computed. We will control for relevant staff- and client-level variables. Additional analyses may include testing whether client and staff change scores (3-month survey score subtracted from pre-test) predict TN-ROCS program-level outcomes such as retention and disciplinary infractions. Significant effects will be designated by *p* < 0.10 and meaningful effect size estimates.

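### The only effect size named, omega squared from a four-timepoint ANOVA, is on its natural reading unsigned and omnibus, so it does not measure the baseline-to-3-month change that defines the primary effectiveness outcomes

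*Protocol article*

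**What the plan says.** Under Primary staff outcomes the article states the target: "We will examine change from the baseline to the three-month follow-up timepoint in the following measures". Primary client outcomes has the same sentence for clients: "We will examine change from the baseline to the 3-month follow-up timepoint in the following measures".

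The Effectiveness section of the data analysis plan analyses these measures with "repeated measures factorial ANOVAs that compare pre, post-, 1-month, and 3-month follow-up data for clients and staff". Tukey post hoc comparisons between timepoints follow. One effect size is then named: "Omega squared effect size estimates will be computed". No contrast, no partial or total version and no interval is attached to it. The section closes with a rule under which an effect counts as significant if p < 0.10 "and meaningful effect size estimates". The rule states no direction.

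Two other statements bear on the point. The same section defines a 3-month change score, but only as a predictor in further analyses that may be run. Study design overview describes the effectiveness goal as change across all four assessment points.

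**The concern.** The outcome is a signed difference between two timepoints, while the effect size used to judge it is a share of variance over four. A share of variance cannot be negative in the population, so improvement and deterioration of the same size look identical. It also credits movement at post-test or 1 month that has disappeared by 3 months.

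Sign matters here because the scales point in different directions. Higher scores are favourable on the Perspectives on Stigma Reduction, Social Distance and Attitudes Toward Prisoners measures. They are unfavourable on Difference and Disdain, the Substance Abuse Self-Stigma Scale and the Internalized Shame Scale. A table of omega squared values across these measures does not show which ones moved the right way.

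Durability matters because staff get the post-test link at the end of the training, and the Discussion hopes to learn which training elements stick. What is at stake is whether the stated rule for declaring an effect answers the stated question.

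**Working it through.** The article gives no expected omega squared, power or target effect, so there is no figure to reproduce. The property of the measure was checked directly.

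**Inputs from the article.** Four timepoints; 72 staff with 75% retained at 3 months (72 × 0.75 = 54); 72 clients with 50% retained (72 × 0.50 = 36).

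**Assumptions, not in the article.** Outcome SD = 1 at each wave; equal within-person correlation rho of 0.5 or 0.7; effect size d = 0.4 SD.

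**Formula.** Let SS be the sum of squared deviations of the four wave means from their average, and s² = SS/4. Population partial omega squared for time is s²/(s² + 1 − rho).

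**Sums of squares.**
- Lasting gain (0, d, d, d): the average is 0.75d, so SS = (0.75² + 3 × 0.25²)d² = 0.75d².
- Bump gone by 1 month (0, d, 0, 0): the average is 0.25d, so SS = (0.75² + 3 × 0.25²)d² = 0.75d².
- Bump gone only by 3 months (0, d, d, 0): the average is 0.5d, so SS = 4 × 0.5²d² = 1.00d².

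**Partial omega squared at d = 0.4.** For the lasting gain, s² = 0.75 × 0.16/4 = 0.030. This gives 0.030/0.530 = 0.057 at rho 0.5 and 0.030/0.330 = 0.091 at rho 0.7. For (0, d, d, 0), s² = 0.040, giving 0.040/0.540 = 0.074 and 0.040/0.340 = 0.118.

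| Wave means | SS/d² | rho 0.5 | rho 0.7 | Change at 3 months |
|---|---|---|---|---|
| Lasting gain (0, d, d, d) | 0.75 | 0.057 | 0.091 | +0.40 SD |
| Worsening (0, −d, −d, −d) | 0.75 | 0.057 | 0.091 | −0.40 SD |
| Bump gone by 1 month (0, d, 0, 0) | 0.75 | 0.057 | 0.091 | 0 |
| Bump gone by 3 months (0, d, d, 0) | 1.00 | 0.074 | 0.118 | 0 |
| Fading bump (0, d, d/2, 0) | 0.69 | 0.052 | 0.084 | 0 |
| Linear gain (0, d/3, 2d/3, d) | 0.56 | 0.043 | 0.069 | +0.40 SD |

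For a common d the ordering follows from SS alone, so it does not depend on d or rho. It also holds for the total version, s²/(s² + 1): 0.030/1.030 = 0.029 for the lasting gain against 0.040/1.040 = 0.038 for (0, d, d, 0).

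**Sample estimates.** Simulation (4,000 runs, rho 0.5) gave means for the first four rows of 0.057, 0.056, 0.056 and 0.073 at n = 36, and 0.056, 0.056, 0.057 and 0.074 at n = 54.

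**What the signed change would offer.** The SD of change is √(2(1 − rho)), which is 1.00 at rho 0.5 and 0.77 at rho 0.7. The 90% half-width for 36 clients is 1.69 × 1.00/√36 = 0.28 SD, or 1.69 × 0.77/√36 = 0.22 SD. For 54 staff it is 1.67 × 1.00/√54 = 0.23 SD, or 1.67 × 0.77/√54 = 0.18 SD. With such intervals a change of +0.40 SD is distinguishable from zero and from −0.40 SD.

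**The case against.** The strongest reply is that direction and the 3-month contrast are already in the plan. The Tukey comparisons include baseline against 3 months and show which mean is higher. Preliminary analyses lists means: "We will run descriptive statistics (i.e., ranges, means, frequencies"). The direction of scoring is stated for most scales. A worsening or a vanished bump would therefore be visible in the planned output. This stands, and it limits the consequence: the information is not lost. But the Tukey comparisons serve to locate differences between timepoints. They are not the effect size that the rule relies on.

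The four-timepoint goal in Study design overview also fits an omnibus effect size. That is a reason to keep omega squared for that goal, but not to use it for outcomes defined at 3 months. Nor does the article state that omega squared will be the omnibus time effect; it could be computed for a single contrast. It would then isolate the contrast but still lack a sign.

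Not every vanished bump outranks a lasting gain. At equal peaks the fading shape (0, d, d/2, 0) scores slightly lower, 0.69 against 0.75 d squared, though still above a linear gain at 0.56.

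A reader might infer three stronger things that the article does not support:
- That omega squared is the figure that will size the randomized trial. The abstract says only that "results will be used to inform a larger, randomized controlled trial", and no section assigns omega squared that use.
- That the signed pre-post change could serve as that trial's between-arm effect. Potential limitations says that the lack of a control group restricts conclusions about effectiveness and that change may be attributed to the surrounding program.
- That SDs will not be reported because the descriptive list omits them. A condensed article may leave such detail to the full plan.

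**Conclusion.** The point holds as a mismatch between outcome and effect measure. The only named effect size, and hence the one in the decision rule, cannot tell a lasting gain from an equal worsening or from a bump gone by 1 month (0.75 d squared each). It ranks a bump gone only by 3 months above the lasting gain (1.00 against 0.75 d squared). At d = 0.4 SD that is 0.074 against 0.057 at rho 0.5, and 0.118 against 0.091 at rho 0.7.

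The ordering is arithmetic for effects of equal d. The omega squared values rest on the assumed d and rho, and the whole point rests on reading omega squared as the effect of time over four waves. The absence of sign does not depend on that reading. Whether a short-lived bump will occur is not known from the article. The practical consequence is moderate: the study's main goal is feasibility, and the Tukey output would alert a careful reader.

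**What to change.** For each primary staff and client outcome:
- Report the mean change from baseline to 3 months in scale points, with sign and a 90% interval to match p < 0.10.
- Report the standardized change and say which SD was used.
- State which direction is favourable. The change score in the Effectiveness section subtracts the 3-month score from the pre-test score, so a rise comes out negative; fix one convention.
- Apply the meaningful-effect-size half of the rule to this signed change.
- Keep omega squared as a supplementary figure for the time effect over four timepoints, and say whether it is the partial or total version.

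The SD of change and the baseline-to-3-month correlation may be added as planning inputs for later work, without presenting the uncontrolled change as a between-arm effect.

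The cost is a few sentences in the analysis plan and a few columns in the results table. No new data are needed.

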#### Data protection and monitoring

All research ethics and HIPAA protocols will be followed during the trial to protect the confidentiality of client and staff data. Any significant changes to the trial protocol will be communicated to the institution’s IRB and approved prior to implementing. Such changes will also be reflected in the clinicaltrials.gov registry. Adverse events are queried at each client baseline and follow-up interview; any that occur during the trial will be reported to the IRB. After the data is analyzed, results will be communicated to the sponsor and used to finalize the CSTARR treatment manual containing the staff and client interventions.

## Discussion

Stigma creates significant barriers to receiving addiction care within the legal system and must be addressed in order to increase the uptake of evidence-based programs and ultimately improve legal and recovery outcomes for people involved in the criminal legal system. However, there are no interventions currently targeting stigma tied to substance use and criminal involvement among staff or clients within the criminal legal system, which is a uniquely complex and challenging implementation setting for stigma reduction. Our study begins to address this major gap by providing pilot data on a promising set of interventions for legal system staff and clients that address stigma tied to addiction and criminal involvement. Our interventions are well-grounded in the science of stigma reduction and our team has the relevant expertise in stigma, addiction, and criminal legal intervention implementation to accomplish this project.

The primary goal of this study is to determine how feasible it is to implement a suite of interventions in a multi-level framework within the criminal legal system, both from staff and client perspectives, and to gauge how acceptable the intervention content is to staff and clients. Through gathering staff and client anonymous feedback on our intervention content, we will identify which aspects of the intervention are most meaningful and impactful, which aspects need further refining, and whether the structure and delivery of the interventions work well (e.g., length of training, virtual format). For example, this study will be the first to demonstrate the value of involving a person with lived experience of addiction and incarceration in a stigma reduction training for criminal legal staff. Moreover, this study will be the first to demonstrate the utility of a client self-stigma intervention targeting both addiction and criminal involvement. We hope that the results of this study will indicate which elements of the staff training “stick” to improve attitudes and behaviors toward legally-involved people with SUDs, and which aspects of the self-stigma intervention are most helpful for clients as they move throughout the TN-ROCS program. Additionally, we hope to observe improvements in staff stigmatizing attitudes and willingness to engage in behaviors that are more supportive (vs. punitive and stigmatizing) toward the clients they work with, as well as improvements in client self-efficacy, coping skills, and self-stigma. One of the primary deliverables of this project will be a finalized manual and set of survey instruments to be examined as part of a more rigorous randomized controlled trial.

Through stigma reduction at the social/public and self levels within the criminal legal system, we hope to impact the culture to be more supportive of addiction treatment. In addition, we hope this study begins to bring awareness to the pervasive and damaging structural stigma surrounding addiction and criminal involvement. For example, even with improved acceptability of addiction treatment by staff and better engagement in treatment among clients, the criminal legal culture cannot change without broader acceptance of people with criminal/addiction histories in our society. This is necessary to facilitate better allocation of funding to research these issues and better treatment of these individuals within our healthcare and other systems. The criminal legal context is a starting point where stigma reduction has the potential to be impactful, but it is the tip of the iceberg.

### Potential limitations

Although this is the only multi-level stigma intervention being developed and tested thus far within the criminal legal system, there are limitations to our study design. Because we are working with staff and clients within a single program (i.e., TN-ROCS) in a single region of the U.S., we are limited in what we can generalize to other geographic areas or drug recovery programs. In particular, the region this study is being implemented in is largely composed of people identifying as non-Hispanic white, which means that future studies that include people of color will be needed to refine intervention content and ensure its generalizability to more diverse groups. Moreover, all clients taking part in TN-ROCS were mandated, and this study’s results may not generalize to samples of legally-involved people entering substance use treatment voluntarily; potential differences in the implementation and impact of CSTARR with legally-involved clients voluntarily enrolled in treatment should be examined in future research. In addition, we make an assumption that clients and staff interact with each other during this study, but we do not gather direct evidence of this. This is an eligibility criterion for staff (must have had interacted with TN-ROCS clients in the past 90 days), and the structure of the program requires that clients appear before the judge as well as other members of the TN-ROCS team on a regular basis to monitor their progress in the program. However, we will not be able to ensure whether or not the clients we are delivering the interventions to have interacted with the staff that participated in the staff trainings, and vice versa. This limits our ability to draw conclusions about the trickle-down impacts of social/public stigma reduction on client-level outcomes. Further, not having a control group limits our ability to draw conclusions about this treatment’s effectiveness, and because our multi-level intervention is being implemented within the context of another set of interventions (i.e., TN-ROCS provides a range of substance use treatments), it is possible that our outcomes will be attributed to TN-ROCS rather than the stigma interventions. Finally, our outcome measures are limited in the sense that they are all self-reported, which is not ideal for assessing things like urine drug analysis results. Also, due to the dearth of research on criminal involvement stigma, our stigma measures were largely validated for substance use stigma only. The psychometric properties of all adapted measures will be examined as part of the data analysis process. These are important factors we will take into consideration in a more rigorous randomized controlled trial of this intervention. Additionally, we anticipate a great deal of heterogeneity in client-level intervention implementation across counties due to differences in size of the TN-ROCS program, court schedules, logistics, and support from CJLs. Our ability to combine pre-, post- and follow-up data across counties to gauge the preliminary effectiveness of the client-level intervention will be limited. Finally, we expect to encounter a variety of logistical challenges with the virtual delivery of interventions that will speak to the feasibility of our design but also inform the methods of a larger, controlled trial.
